### Study Design

This is a diagnostic agreement study, as VE is not considered a gold standard in this setting [23]. Dental caries in this study is defined as primary coronal caries. Data sources (age at dental visit, sex, VE data, and 3D models) will be retrospectively sourced from a sample of children who underwent VE using the ICDAS and intraoral scanning with the TRIOS 4 to produce 3D digital models.

The 3D models for each eligible participant will be subject to an on-screen assessment by 4 qualified dental practitioners. Each practitioner will examine all 3D models at 2 separate time points. An on-screen assessment of 3D models based on tissue geometry and approximate natural colors (excitation to visible white light) will take place first (Figure 1A), followed by an on-screen assessment with the addition of fluorescence texture (excitation to light at 415 nm; Figure 1B). An interval of at least 4 weeks will follow to minimize recall bias before the on-screen assessment process is replicated. Occlusal surfaces of primary molars will be examined using the automated caries scoring system at a single time point only (Figure 1C). Examiners will be blinded to all clinical examination data and automated caries scores when scoring the 3D scans.

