### Statistical Analysis

Data checking and cleaning will take place before analysis. Descriptive statistics for patient characteristics such as age, sex, caries prevalence, and the proportion of children with enamel defects will be reported. The total number of tooth sites included in the analysis will be reported.

Descriptive characteristics for the rater population will be reported, including qualification, clinical background, years of experience, and training results for each rater. Interrater and intrarater reliability for on-screen assessment of 3D models based on color and fluorescence using the intraclass correlation coefficient will be reported for all examiners. These estimates will be obtained from a multilevel model fitted to the surface-level data, accounting clustering (see below), and zero inflation.

To assess agreement among methods, we will undertake both surface-level and individual-level analyses. At the surface level, caries data naturally have 3 levels with surfaces clustered within a tooth, which are clustered within an individual. Therefore, for this analysis, we will use multilevel logistic regression to estimate method agreement while accounting for clustering for the tooth. Specifically, separate multilevel models will be fitted to compare VE with each of the alternative methods by including the variable method (VE vs on-screen assessment of 3D models in approximate natural colors, on-screen assessment of 3D models in approximate natural colors featuring fluorescence, and automated system) as the fixed effect. The coefficient estimates for the variable method will be used to indicate the level of agreement. The multilevel model will be fitted with a zero-inflated binomial distribution.

At the individual level, a numerical variable representing the number of lesions per individual will be generated and analyzed with 2 approaches. First, Bland-Altman method agreement analysis will be performed using a regression approach. Specifically, a model will be constructed to regress the difference between each pair of methods on their average [36]. The analysis will be repeated for each possible pair of methods. Second, for each possible pair of methods, an intraclass correlation coefficient will be estimated from a multilevel model fitted to the paired data consisting of the 2 measures for each individual obtained from the 2 methods, fitted with a zero-inflated Poisson distribution.

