## Discussion

This protocol aims to fill a knowledge gap by describing an approach for determining the diagnostic agreement between VE using ICDAS and on-screen assessment of 3D models featuring fluorescence obtained with an IOS.

Intraoral scanning is increasingly being adopted in dentistry as it offers improved clinical workflows for patient assessment and treatment planning, particularly in the disciplines of prosthodontics, orthodontics, and periodontics [13,38,39]. The role of scanning technology in supporting clinical diagnostics is an emerging research area [19,20,40-43]. There is paucity in the literature describing on-screen assessment of 3D models as a method for caries detection.

A strength of our study is the consideration of different approaches to analyze agreement. Our use of multilevel generalized linear regression models to analyze surface-level dental caries data has several strengths. First, caries from the same individual are more correlated than those between individuals. If this clustering is ignored, the estimated variance may be misleadingly small [44]. We will use multilevel models that account for clustering. Second, the multilevel regression approach allows for estimating method agreement while accounting for variability due to the influence of the rater and timing of assessment [45]. Finally, because all eligible primary teeth surfaces will be analyzed the high proportion of sound surfaces will result in zero-inflated outcome data. We will address this by fitting a generalized linear regression framework allowing the use of a zero-inflated binomial distribution; whereas traditional agreement methods, such as the κ statistic, are limited in this context [46]. A limitation of the statistical approach is that the coefficient estimates derived from the multilevel model do not quantify absolute agreement. As an alternative analysis, we will analyze the total caries at the individual level with a regression-based Bland-Altman agreement analysis [36]. The excess of zeros and, hence, the nonnormal distribution of the data precludes the calculation of the limit of agreement estimates that are clinically interpretable. Consequently, we will use the intraclass correlation coefficient derived from a multilevel model fitted with a zero-inflated Poisson distribution, acknowledging that this is influenced by the variability in the population.

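### The two visual-versus-on-screen models name no surface-level effect, so the method coefficient is pulled toward zero and its standard error can be wrong in either direction

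*Protocol article*

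**What the plan says.** The Statistical Analysis section of the protocol article recognises that "caries data naturally have 3 levels with surfaces clustered within a tooth, which are clustered within an individual". It then says that "we will use multilevel logistic regression to estimate method agreement while accounting for clustering for the tooth", that "separate multilevel models will be fitted to compare VE with each of the alternative methods", and that "The coefficient estimates for the variable method will be used to indicate the level of agreement". The distribution is to be zero-inflated binomial.

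The Study Design section fixes how many readings each surface receives. For on-screen assessment there are four practitioners, and "Each practitioner will examine all 3D models at 2 separate time points". That is 4 x 2 = 8 readings per surface for each display mode, against one VE reading. For the automated system, "Occlusal surfaces of primary molars will be examined using the automated caries scoring system at a single time point only".

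Pairing is mentioned only for the lesion count per child, where the intraclass correlation comes from "a multilevel model fitted to the paired data consisting of the 2 measures for each individual obtained from the 2 methods". Rater and timing are named as fixed effects only in the sensitivity analysis that compares colour with fluorescence, not in the models that involve VE. On clustering of caries within an individual, the Discussion warns: "If this clustering is ignored, the estimated variance may be misleadingly small".

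**The concern.** The observations in a VE-versus-on-screen model are readings, not surfaces. Readings lie within surfaces, surfaces within teeth and teeth within children, which makes four levels where the plan counts three. The missing link is the one on which the comparison is paired, because VE and the scan are read on the same surface.

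With a tooth effect (and a child effect) but no surface effect, two things follow for the two on-screen models.

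- **The coefficient.** In a logistic model, a log-odds shift averaged over unmodelled surface differences is smaller than the shift for a given surface. The plan reads the coefficient as agreement, so a smaller value looks like closer agreement.
- **The standard error.** It is computed as if readings of one surface were independent given the tooth. Unmodelled pairing tends to make it too wide. Unmodelled examiner or child variation in the method effect makes it too narrow.

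The first objective compares on-screen assessment with and without fluorescence, and the second brings in the automated system. Coefficients on different scales do not support reading these comparisons side by side.

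**Working it through.** The protocol gives no figure to reproduce here, so the check is by simulation.

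**Inputs from the protocol:** 213 participants (Results); 4 examiners x 2 readings (Study Design); one occlusal surface per primary molar in the automated comparison (Study Design; Tooth Surface Exclusion Criteria).

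**Assumptions, not in the protocol:** 20 teeth x 4 surfaces per child; VE prevalence about 4% to 6%; tooth SD 1.5 on the logit scale; surface SD 0 to 3; surface-specific method shift 0.5; no child intercept and no zero-inflation part.

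**Step 1. One VE reading against one on-screen reading.** The shortfall is (0.5 - coefficient)/0.5. The ratio is the mean model SE divided by the actual sampling SD over 60 replicates. The last column adds a surface intercept (12 replicates).

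| Surface SD | Tooth-only coefficient | Shortfall | Model SE | Sampling SD | Ratio | Coefficient with surface intercept |
|---|---|---|---|---|---|---|
| 0 | 0.495 | 1% | 0.0524 | 0.0489 | 1.07 | 0.505 |
| 1 | 0.446 | 11% | 0.0512 | 0.0473 | 1.08 | 0.488 |
| 2 | 0.376 | 25% | 0.0483 | 0.0432 | 1.12 | 0.499 |
| 3 | 0.314 | 37% | 0.0468 | 0.0336 | 1.39 | 0.514 |

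A second, separate simulation of the tooth-only model gave 0.47, 0.39 and 0.29 at surface SD 1, 2 and 3, which are shortfalls of 6%, 22% and 42%. Its SE ratio was 0.99 to 1.21.

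An SD estimated from 60 replicates has a relative error of about 1/sqrt(2 x 59) = 9%. Ratios of 1.07 to 1.12 are therefore within noise of 1. Only the value at surface SD 3 stands clear of it.

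At surface SD 2 the tooth-only z is 0.376/0.0483 = 7.8, against 0.496/0.0562 = 8.8 for matched pairs. The loss is real but modest.

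**Step 2. One VE reading against eight on-screen readings, surface SD 2, tooth-only model.** The model SE is 0.0385 throughout (80 replicates).

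- Identical examiners, no child variation in the method effect: sampling SD 0.0319, ratio 1.21. The second simulation gave about 1.0 for eight readings.
- Examiner SD 0.3 (logit): sampling SD 0.1137, ratio 0.34.
- Examiner SD 0.5: sampling SD 0.2128, ratio 0.18.
- Child-by-method SD 0.5, identical examiners: sampling SD 0.0493, ratio 0.78.

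A hand check on the examiner rows: the mean of four examiners with SD 0.3 has SD 0.3/sqrt(4) = 0.15. Scaled by the attenuation 0.388/0.5 = 0.78 this is 0.116. Combined with the sampling part it is sqrt(0.116^2 + 0.032^2) = 0.120, close to 0.1137. These rows apply when inference is meant to reach beyond the four examiners.

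**Step 3. Automated model, one occlusal surface on each of 8 molars, read once.** The tooth intercept gives 0.495 (SE 0.142, sampling SD 0.143), and matched pairs give 0.495 (SE 0.142). Tooth and surface are the same unit here, so tooth clustering is exact pairing.

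**Step 4. Scale.** At surface SD 2 the same shift of 0.5 appears as an odds ratio of exp(0.495) = 1.64 in the automated model and exp(0.376) = 1.46 in an on-screen model.

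**The case against.** **A change of estimand, not a bias.** The shrinkage is the usual non-collapsibility of the log-odds ratio, and 0.5 is the true value only because the simulation defines it per surface. This largely stands. A shift of zero stays zero under either model, and an averaged coefficient is a legitimate quantity. What remains is that the plan does not say which quantity it means, and its one specification yields different scales for the on-screen and automated models.

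**The surface-specific coefficient does not measure agreement either.** This also stands. It measures a systematic shift, and the Discussion concedes that these coefficients do not quantify absolute agreement and adds individual-level analyses. That favours reporting discordant counts alongside it.

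**An article condenses, and a surface effect is not excluded.** This stands in part. The article does set out the levels, the clustering unit and the quantity to be read, and a literal reading omits the surface.

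**Stronger readings that the documents do not support.**

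- A reader might infer that the error bars are always too wide and that a large share of the information is lost. Step 1 shows little excess except at the largest surface SD, and Step 2 shows the opposite once examiners or children vary.
- A reader might infer that the two readings are wholly unpaired. The shared tooth effect links them in part.
- A reader might extend the point to all three VE comparisons. The automated one is exempt.
- A reader might take the Discussion's warning about variance to be mistaken, or child clustering to be ignored. The warning concerns clustering within an individual and is correct for that, and the Discussion says that clustering will be accounted for.

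**Conclusion.** The concern holds for the two VE-versus-on-screen models only. As written, they leave out the unit on which the comparison is paired. The coefficient read as agreement is then smaller than the surface-specific shift, by roughly 6% to 42% for an assumed surface SD of 1 to 3, and it is not comparable with the automated model's coefficient. The standard error is not secured: in these simulations it ran from about right to 1.39 times the sampling SD without examiner or child variation, and from 0.18 to 0.78 times with it.

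The direction of the shrinkage does not depend on the assumptions, but every size does. Neither the zero-inflation part nor the study's real variance components were available to the check, and it assumes that all eight readings enter the model. This should be put right before the on-screen data are analysed, but it does not invalidate the study.

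**What to change.** For the two on-screen models, state the structure as readings within surface within tooth within child by adding a surface random intercept, and include a rater term. Say how the eight readings enter, and whether inference is to these four examiners or to examiners in general. The automated model needs no surface term.

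Alternatively, report the paired surface-level difference in the proportion positive, (surfaces positive on screen only - surfaces positive on VE only)/surfaces compared, with both discordant counts shown and robust or bootstrap standard errors at the level of the child. Showing it by examiner keeps examiner differences visible, which resampling children alone would not capture.

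The cost is a change of analysis wording. Surfaces are already scored individually, so no new data are needed. The extra random effect slows fitting, and the paired-difference version avoids that.

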Recent advances have seen the development of computational methods as a more objective measure to quantify dental caries and support clinical diagnosis. TRIOS has developed an automated caries scoring system for their software that can automatically classify caries on occlusal surfaces based on color and fluorescence changes (TRIOS Patient Monitoring [TPM]; version 2.3; 3Shape TRIOS A/S) [16]. When comparing the diagnostic performance as quantified by the area under the curve (AUC), early in vitro and in vivo validation studies suggest that the automated score is comparable to VE at the early (AUC VE 0.71 vs 0.76) and moderate disease thresholds (AUC VE 0.90 vs 0.90), based on a histological reference standard for permanent teeth [20]. A separate investigation into the validity of this algorithm in primary teeth concluded it had comparable performance (AUC 0.88) to VE (AUC 0.96) for caries detection of primary tooth occlusal surfaces [21]. The latter was a small in vitro feasibility study; consequently, results should be interpreted cautiously and not generalized to the clinical setting. The in vivo performance of automated assessment of 3D models for caries detection in primary teeth has yet to be established.

One of the problems with investigating early caries detection methods in realistic settings is the choice of a reference standard for method comparison, as histological or operative references are rarely feasible or ethical. It is argued that when VE alone is used as a gold standard, measures of diagnostic accuracy (sensitivity and specificity) may overestimate the true accuracy of the caries detection method under investigation [22,23]. Instead, reporting on the diagnostic agreement has been suggested to be more appropriate. Diagnostic agreement quantifies the similarity between methods in detecting the outcome of interest to be used interchangeably [24].

This study describes the protocol and statistical analysis plan for determining the diagnostic agreement between VE, on-screen, and automated caries detection methods using 3D models in children.

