## Methods

### Aims and Objectives

The specific study objectives are to, first, determine and compare the diagnostic agreement between VE and on-screen visual assessment of 3D models in approximate natural colors with and without fluorescence to detect and classify carious lesions on visible tooth surfaces in primary teeth. The second objective is to determine the diagnostic agreement between VE and the automated caries scoring system for detecting and classifying occlusal carious lesions in primary teeth. Finally, the third objective is to explore the impact of caries threshold, tooth surface examined (smooth vs occlusal), and enamel defects’ presence on the reported agreement estimates between caries detection methods.

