### Outcome Measures

For agreement analyses, ICDAS and modified ICDAS codes will be collapsed for each surface into four categories labeled sound surface (0), initial caries (1), moderate (2), and extensive caries (3). A binary dental caries variable will be created for each surface, and the detection threshold will be initial caries (0 vs 1, 2, and 3).

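### The surface-level agreement measure is a method coefficient that captures only relative bias, and no planned between-method statistic measures surface concordance within a child

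*Protocol article*

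**What the plan says.** The Introduction of the Protocol article (Intraoral Scanners for Dental Caries Detection) defines the target: "Diagnostic agreement quantifies the similarity between methods in detecting the outcome of interest to be used interchangeably". The first objective is to "determine and compare the diagnostic agreement between VE and on-screen visual assessment of 3D models", with and without fluorescence.

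Under Outcome Measures, "A binary dental caries variable will be created for each surface", with initial caries as the main threshold. Under Statistical Analysis, "we will use multilevel logistic regression to estimate method agreement while accounting for clustering for the tooth". The structure is then given: "separate multilevel models will be fitted to compare VE with each of the alternative methods by including the variable method" as the fixed effect. The measure is fixed by "The coefficient estimates for the variable method will be used to indicate the level of agreement", and "The multilevel model will be fitted with a zero-inflated binomial distribution".

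Between methods, the only other planned statistics use lesion totals per child: a regression-based Bland-Altman analysis and an intraclass correlation (ICC) from a zero-inflated Poisson model, each for every pair of methods. The ICC fitted to surface-level data is for inter- and intrarater reliability of on-screen scoring, not for agreement between methods.

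The Discussion concedes: "A limitation of the statistical approach is that the coefficient estimates derived from the multilevel model do not quantify absolute agreement". It sets kappa aside because most surfaces are sound, and offers the per-child totals as the alternative.

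**The concern.** With method as the fixed effect and caries (yes/no) as the outcome, the coefficient says whether one method flags more surfaces than the other. It does not say whether the two flag the same surfaces. A value of zero is necessary for agreement but not sufficient.

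The stake is the study's central question, whether 3D models can stand in for VE in detecting and classifying lesions on particular surfaces. A coefficient near zero could be read as good surface-level agreement when the lesions flagged are largely different ones. The analyses by threshold, surface location and enamel defects reuse the same model, so they describe how relative bias varies, not how concordance varies.

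**Working it through.** The article states no agreement figure to reproduce. The check is algebra, then an illustration, then a simulation.

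**Inputs.** From the article: 213 eligible participants (Results); a binary outcome per surface; a logistic model with method as the fixed effect and clustering by tooth. Assumed, because the article gives no figures: 70 surfaces per child and 5% of surfaces flagged for the illustration; 20 primary teeth with 4 surfaces each and about 3% to 18% flagged for the simulation. One reading per method is used throughout.

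**Algebra.** Let each method flag a proportion p of the same N surfaces, and let a fraction f of the surfaces flagged by one method also be flagged by the other.

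- Log odds ratio for method = logit(p) − logit(p) = 0 for every f.
- Positive agreement = 2a/(2a + b + c) = 2fpN/(2pN) = f, where a is the number flagged by both and b + c the number flagged by one only.
- Negative agreement = 2d/(2d + b + c) = 1 − p(1 − f)/(1 − p), where d is the number flagged by neither.
- Kappa = (f − p)/(1 − p).

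A random intercept for tooth does not change this. Given the intercept, the likelihood depends only on how many surfaces each method flags in a tooth, not on which ones. With a surface-level random effect, the coefficient reflects the balance of discordant pairs, as in McNemar's test. Equal discordance in both directions gives zero, however much discordance there is.

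**Illustration.** N = 213 × 70 = 14,910; flagged by each method = 745, so p = 745/14,910 = 0.05.

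| Overlap f | Method log OR | Positive agreement | Negative agreement | Kappa |
|---|---|---|---|---|
| 100% | 0.00 | 1.00 | 1.00 | 1.00 |
| 50% | 0.00 | 0.50 | 1 − 0.05 × 0.50/0.95 = 0.97 | 0.45/0.95 = 0.47 |
| 5% | 0.00 | 0.05 | 1 − 0.05 × 0.95/0.95 = 0.95 | 0/0.95 = 0.00 |
| 0% | 0.00 | 0.00 | 1 − 0.05/0.95 = 0.95 | −0.05/0.95 = −0.05 |

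**Simulation.** 213 × 20 × 4 = 17,040 surfaces, fitted by a marginal logistic model and by a tooth random-intercept logistic model.

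- Identical calls: method odds ratio 1.000 in both models; positive agreement 1.00.
- No overlap, with the same number flagged in the same teeth: odds ratio 1.000 in both models; positive agreement 0.00; kappa −0.03, −0.08, −0.11 and −0.22 at 3.0%, 7.0%, 10.2% and 17.8% flagged.
- No overlap, with the same number flagged anywhere in the child's mouth: odds ratio again 1.000 in both models; positive agreement 0.00.
- Second method flags a random 70% of the VE-positive surfaces and no others: positive agreement about 0.82 (expected 2 × 0.7/1.7 = 0.82) and kappa 0.79 to 0.82, but odds ratio 0.65 to 0.70 (marginal) or 0.60 to 0.63 (tooth random intercept). Judged by the coefficient, this pair agrees less well than the pairs with no overlap.

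The zero-inflation part was not fitted. When each tooth has equal counts from the two methods, swapping the method labels leaves the counts unchanged, so the zero coefficient carries over as long as the zero-inflation part has no surface-specific term.

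**Child totals.** In the same-tooth case with no overlap, the per-child totals were identical: mean difference 0, SD 0, correlation 1. Bland-Altman and ICC on totals cannot see this disagreement. The same holds wherever the two counts match within each child.

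**First objective.** VE-colour and VE-fluorescence are modelled separately. The sensitivity paragraph of Statistical Analysis compares colour with fluorescence directly, which is a different quantity from the difference between their agreements with VE.

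**The case against.** Several points on the other side have weight.

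- **The child-level analyses do respond to some disagreement.** A reader might infer that no planned between-method statistic reacts to which surfaces are called carious. The article does not support that: if discordant calls fall in different children, the totals diverge, and both the ICC and Bland-Altman react. The gap is confined to concordance within a child.
- **Colour and fluorescence are compared.** A reader might infer that nothing bears on the comparison in the first objective. In fact a direct colour-versus-fluorescence analysis is planned, with rater and timing as fixed effects, and the pairwise child-level results can be set side by side. What is not stated is a formal contrast of the two agreements with VE.
- **The limitation is disclosed.** This stands, but disclosure does not repair it. The coefficient remains the stated indicator of the level of agreement, and the alternative offered has its own blind spot within the child.
- **Kappa was set aside for a reason.** That reason does not reach positive and negative specific agreement, which are not chance-corrected and stay interpretable when most surfaces are sound.
- **The extreme overlaps are unlikely.** Examiners are calibrated to weighted kappa above 0.8 for VE and above 0.7 on screen, so overlap near 0% is not a forecast. The 50% row makes the same point less dramatically.

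**Conclusion.** The point holds in this form. The planned surface-level coefficient measures relative bias, and no planned between-method statistic measures surface concordance within a child. With equal numbers flagged, the logistic method coefficient is zero at any overlap while positive agreement runs from 0 to 1. This does not depend on the assumed number of surfaces or prevalence. The kappa and negative-agreement figures do depend on prevalence and are illustrative only. The misleading zero needs the two methods to flag similar numbers. When they do not, the coefficient is non-zero but still does not describe overlap.

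A reader might go further and conclude that the study would declare agreement where there is none. The article sets no threshold for such a declaration and describes the work as a proof of concept, so that is not supported. The supported conclusion is that the surface-level result, as labelled, cannot carry a statement about interchangeability, and that the comparison in the first objective lacks a stated formal contrast.

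**What to change.** 1. Keep the method coefficient but label it relative bias, including where it is used by threshold, surface location and enamel defect.
2. Add a surface-level concordance measure from the paired cross-classification of the same surface by VE and each alternative method: positive agreement 2a/(2a + b + c) and negative agreement 2d/(2d + b + c).
3. Fix the rule for multiple readings. Each on-screen mode has 4 examiners × 2 time points = 8 readings per surface against one VE reading. Compute the measure for each examiner and time point and average over readings. The automated system has one reading.
4. Obtain 95% confidence intervals by bootstrap resampling of children, keeping all teeth, surfaces and readings of a child together.
5. For the first objective, report the paired difference (fluorescence-VE agreement minus colour-VE agreement) with its interval from the same bootstrap.

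The cost is a change of wording in the analysis plan and a small amount of extra programming. It uses the readings the design already provides.

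### A zero-inflated binomial is planned for one yes/no caries call per surface, so the size of the method coefficient rests on a parameter the data identify weakly or not at all

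*Protocol article*

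**What the plan says.** Under Outcome Measures in the protocol article, the four caries categories are reduced to one indicator per surface: "A binary dental caries variable will be created for each surface, and the detection threshold will be initial caries". Under Statistical Analysis, the surface-level plan reads "we will use multilevel logistic regression to estimate method agreement while accounting for clustering for the tooth". It continues that "separate multilevel models will be fitted to compare VE with each of the alternative methods by including the variable method", and that "The coefficient estimates for the variable method will be used to indicate the level of agreement". The distribution is then fixed: "The multilevel model will be fitted with a zero-inflated binomial distribution". On the hierarchy, the same section notes that "caries data naturally have 3 levels with surfaces clustered within a tooth, which are clustered within an individual", although the sentence naming the model mentions clustering for the tooth only.

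The Discussion gives the reason for the distribution, which is that "the high proportion of sound surfaces will result in zero-inflated outcome data", and lists the choice among the strengths of the approach. No binomial denominator above one is stated for the surface model. Nor are covariates for the zero part, or a structural zero shared by all readings of a surface. For rater reliability, Statistical Analysis says that the intraclass correlations (ICCs) come from a surface-level multilevel model that allows for clustering and zero inflation; it does not name that model's distribution or say whether the outcome is binary or four-category.

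**The concern.** Zero inflation has meaning for counts, where the spread of the non-zero values shows how many zeros the base distribution would produce. A 0/1 variable has no such spread. A large share of sound surfaces is simply a low event probability, which the intercept of an ordinary logistic model already represents. Adding a zero-inflation probability adds a parameter about which the data say nothing, or speak only through the shape assumed for the random effects.

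At stake is the quantity the plan reports as surface-level agreement. If π is free, two analysts with the same data could report clearly different method coefficients, and the likelihood would not tell them apart. The article describes itself in the Introduction as giving both the protocol and the statistical analysis plan, and it states and defends this distribution, so the point is not a detail left to another document.

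**Working it through.** The plan gives no figure to reproduce, so the check is of identifiability. Prevalences, random-effect sizes and surfaces per child below are assumptions. The document supplies the binary outcome, the model form, the 213 participants (Results), and the restriction of the automated score to primary molar occlusal surfaces at one time point (Study Design). The zero part is taken in its usual form, acting on each record separately.

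**1. No random effects.** Let q0 and q1 be the observed prevalences for visual examination and the alternative. The model says q = (1 − π)p, so p = q/(1 − π). Three parameters (π, intercept, method coefficient) face two observed prevalences. Every π below 1 − max(q0, q1) fits equally well, with

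OR = [q1/(1 − π − q1)] / [q0/(1 − π − q0)].

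| Assumed q0 vs q1 | π = 0 | π = 0.5 | π = 0.6 | π = 0.65 |
|---|---|---|---|---|
| 5% vs 7.5% | 1.54 | 1.59 | 1.61 | 1.64 |
| 10% vs 15% | 1.59 | 1.71 | 1.80 | 1.88 |
| 20% vs 30% | 1.71 | 2.25 | 3.00 | 4.50 |

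Worked entry, 20% vs 30% at π = 0.65: (0.30/0.05)/(0.20/0.15) = 6.00/1.333 = 4.50. Along each row the log-likelihood is constant.

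**2. Tooth intercept, automated comparison.** One occlusal surface per molar gives two binary readings per tooth: four cells, hence three degrees of freedom, against four parameters (intercept, method coefficient b, tooth SD, π). Take as true π = 0, intercept −3, b = 0.50, SD = 2. The cells are 0.760 (neither), 0.067 (visual only), 0.110 (automated only) and 0.063 (both), so the prevalences are 0.067 + 0.063 ≈ 13% and 0.110 + 0.063 ≈ 17%. These cells are reproduced to numerical precision by:

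| π | b | exp(b) | Tooth SD | Latent ICC = SD²/(SD² + π²/3) |
|---|---|---|---|---|
| 0 | 0.50 | 1.65 | 2.0 | 0.55 |
| 0.3 | 0.74 | 2.09 | 3.0 | 0.73 |
| 0.4 | 1.01 | 2.75 | 4.1 | 0.83 |
| 0.5 | 2.52 | 12.4 | about 10 | 0.97 |

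(In the ICC formula, π²/3 ≈ 3.29 is the logistic variance, not the zero-inflation probability.) The variance component trades against π as well as the coefficient.

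**3. Normal child intercept, 213 simulated children, true π = 0.** π now becomes formally estimable.
- With 8 surfaces per child, every grid value of π from 0 to 0.4 stays within 3.84 of the minimum deviance. Over that span the OR goes from 2.02 to 2.34 in one data set and from 1.53 to 1.71 in another.
- With 88 surfaces per child, π is held much more tightly: the grid minimum falls at 0.1 in one data set and at 0 in the other.

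**4. As in 3, but with a non-normal child effect (two-class or uniform), true π = 0, true b = 0.50.** In 20 data sets the estimated π was 0.30 to 0.65, and b rose relative to the π = 0 fit in all 20. With 88 surfaces, b was 0.61 to 0.77 with π estimated and 0.41 to 0.54 with π = 0. The likelihood ratio in favour of π > 0 in those 88-surface data sets was 4.7 to 60, so a fit comparison would favour zero inflation where none exists.

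**The case against.** The strongest reply is that the plan specifies a multilevel model, and that with a child-level effect and many surfaces π can be estimated. That stands. A reader might infer that the planned model is simply not identifiable; the document does not support so flat a statement. Exact non-identification holds without random effects, and for the automated comparison with tooth clustering alone. Elsewhere identification is borrowed from the assumed link and random-effect shape.

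A reader might also extend the 5% vs 7.5% row to an OR of 3.00 at π = 0.9 or 9.00 at π = 0.92. The arithmetic is right, but π is limited there to 1 − 0.075 = 0.925, so these values lie at the edge of a model without random effects. When caries is rare and π moderate, the shift is small.

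Nor is the whole inference lost. Without random effects, dividing both prevalences by (1 − π) keeps their order, and equal prevalences give OR = 1 at every π. The sign of the coefficient and the null of no method difference are therefore unaffected in that model.

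The plan names no primary analysis, also plans individual-level analyses that do not use this model, and concedes in the Discussion that the coefficients do not quantify absolute agreement. This reduces reliance on the coefficient but is a different limitation and does not repair it. Finally, four raters at two time points could support a count out of several readings, or a structural zero shared across them, either of which would be identifiable. The article states neither.

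**Conclusion.** The point holds, with limits. As written, the surface-level distribution is wrong for a single binary call, and the stated rationale mistakes low prevalence for zero inflation. What becomes arbitrary or assumption-driven is the size of the method coefficient. In the no-random-effects illustration this ranges from slight (1.54 to 1.64) to large (1.71 to 4.50) for π between 0 and 0.65, depending on assumed prevalence. In the automated comparison with tooth clustering only, identical data support odds ratios of 1.65 and 12.4. These figures rest on assumed prevalences and variances and on a zero part acting record by record; the non-identification in those two cases does not depend on the particular values.

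The rater ICCs are affected only to the extent that zero inflation there means the same model on the binary outcome, which the text leaves open. The zero-inflated Poisson for lesions per child is outside this point.

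**What to change.** - In Statistical Analysis, remove zero inflation from the surface-level method comparisons and fit ordinary Bernoulli multilevel logistic models with child and tooth random intercepts.
- Add a surface intercept only where several surfaces per tooth are read. In the automated comparison there is in effect one occlusal surface per tooth, so tooth and surface intercepts would be aliased.
- Do the same for the rater ICCs if they are computed on the binary outcome, and state which outcome is used.
- In the Discussion, say that a high share of sound surfaces is low prevalence, and no longer list the zero-inflated binomial as a strength.
- If the investigators do want a structural-zero component, they should write out the zero part and its identifying assumption, for example a zero shared by all readings of a surface.

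The cost is a change of model family and a corrected sentence or two. No new data or rescoring is needed. The Results section reports that the automated-score data were already being analysed, so any surface-level fit already made with zero inflation would need to be rerun.
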